### 2.10. Concealment of Allocation

Before preceding to random allocation into either the control or intervention arm of the study, an informed consent/agreement ascertainment and eligibility will be obtained. The allocation will not be known to research assistants, participants, or trial representatives (pharmacists) until the point of randomization. Interventional households will only be known to research assistants. The participants will be introduced to the interventional arm facilitator individually, by mobile phone call. If the pharmacists and research teams are allocated to the control arm, they will continue to regularly contact the allocated UC.

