### 2.4. Data Collector’s Eligibility Criteria and Training

The data collector team will be comprised of healthcare workers (pharmacists, LHWs, and vaccinators). The trained pharmacists will select pharmacies (5 = control, 5 = interventional) to recruit participants, with their full consent (Additional File S2). Leaflets and materials related to the appropriate use of antibiotics will be provided to the participants at the pharmacies.

The data collector team will have the required qualifications, and the pharmacist must be registered with Pakistan Pharmacy Council (PPC) [29]. The pharmacist’s abilities are directly related to the quality of the study, which depends solely on the pharmacist’s competency. Consequently, the pharmacists involved in this study will have experience in previous patient-centered care services at community pharmacies or be engaged with population-based studies.

The pharmacists and other healthcare members must be trained for the counseling sessions with participants at community pharmacies. Effective training in communication skills will be held before the execution of the trials, and pseudo-patient training will be arranged to assess their counseling skills at community pharmacies. Finally, the principal investigator will approve the trained team for the trial.

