### 2.8. Recruitment of the Participants

#### Inclusion Criteria

Once their complete consent has been given, patients diagnosed with LRTIs (Table 1) will be screened for the inclusion criteria at the pharmacy. Poor adherence to recommended antibiotics for LRTIs, adult patient family members (age > 18 years), irrespective of gender, living in the UC for the last 1 year, and ability to speak and comprehend Urdu/Pushto or English are among the study’s qualifying requirements. Participants in the study group should have no extra comorbidities and have not participated in or been a part of any study/trial related to respiratory tract infections or antibiotics in the previous four months. Those who are unable to independently answer the questions owing to sight/vision, hearing, or cognitive problems, as well as those who do not meet the inclusion criteria, will be excluded (Figure 1).

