### 2.9. Randomization

Using a computer-generated random digit number, a biostatistician will construct a random allocation order that is independent of/blinded to participants and trial size. For every participant that is recruited, a sample 1:1 is used to allocate them into control and interventional groups. Finally, ten pharmacists will be randomized to the intervention and control arms 1:1 and the permuted method will be used. This will be accomplished by the study teams exchanging a list of pharmacists, each of whom has a unique number assigned to them. The status of allocation will be conveyed to the research team coordinators, who will notify individual pharmacists as soon as the participants’ agreement to trial participation is obtained by research teams.

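### The protocol gives two incompatible accounts of how a patient gets an arm; if the arm follows the pharmacy or pharmacist, the concealment promised in section 2.10 cannot hold

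*Protocol article*

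**What the plan says.** The protocol article contains two sets of statements on allocation.

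**Individual allocation, concealed.** Section 2.2 calls the trial individually randomised. Section 2.9 has a biostatistician prepare the order and states: "For every participant that is recruited, a sample 1:1 is used to allocate them into control and interventional groups". Coordinators then tell pharmacists the allocation once the participant has agreed. Section 2.10 says that before allocation "an informed consent/agreement ascertainment and eligibility will be obtained", and that "The allocation will not be known to research assistants, participants, or trial representatives (pharmacists) until the point of randomization". Table 3 lists duty pharmacists as not aware of allocation.

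**Arm attached to pharmacy or pharmacist.** Section 2.4 states: "The trained pharmacists will select pharmacies (5 = control, 5 = interventional) to recruit participants". Section 2.9, directly after its sentence on individual allocation, states: "ten pharmacists will be randomized to the intervention and control arms 1:1 and the permuted method will be used". Section 2.10 adds: "If the pharmacists and research teams are allocated to the control arm, they will continue to regularly contact the allocated UC".

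On the place of recruitment, section 2.8 says that patients "will be screened for the inclusion criteria at the pharmacy".

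**The concern.** Concealment protects a trial only if the person who decides whether to approach, screen or enrol a patient cannot foresee that patient's arm. If a pharmacy or its pharmacist already carries an arm, holding back the formal notice until consent hides nothing: the place of recruitment gives the arm away.

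Staff could then, knowingly or not, enrol more motivated or more easily reached patients in one arm than in the other. Beliefs, knowledge and adherence, the outcomes in section 2.14, are all plausibly sensitive to such differences. The result would be a difference between arms that exists before any education is given. This is bias in who enters the trial. It is separate from the effect of clustering on standard errors and power, and widening the standard errors does not correct it. The mixed model in section 2.17 adjusts for baseline BMQ and PAS-QA, which removes only the part of the imbalance that those two scores capture.

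**Working it through.** The check is mainly a comparison of statements. No figure in the protocol decides it.

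1. **Can the statements all be true?** Under individual allocation, a patient at any pharmacy has a 0.5 chance of either arm, so a recruiting pharmacy has no arm. Section 2.4 nevertheless gives recruiting pharmacies an arm. The two fit together only if a patient recruited at a control pharmacy can be sent to intervention, and the reverse. No section describes such a transfer.

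2. **What follows if the arm goes with the pharmacy or pharmacist?** The arm of the next patient is then predictable with probability 1, against 0.5 under concealed simple 1:1 allocation. If the pharmacist's own arm is withheld until the first consent, as the notification rule in 2.9 might allow, only that first patient is protected. With ten pharmacists, that is at most 10 of 400 patients.

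3. **Does it help that research teams obtain agreement (2.9)?** Not by itself. Section 2.10 speaks of research teams, too, as allocated to the control arm.

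4. **Does Table 3 settle it?** No. Duty pharmacists are marked unaware of allocation but aware of the pharmacist-led interventions. In a pharmacy that serves one arm only, knowing whether the intervention is delivered there amounts to knowing the allocation.

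5. **How much could selection matter?** The documents give no basis for an estimate. Two illustrations show direction only.
 - *Assumed mix of patients.* Suppose half of eligible patients are willing, with 70% adherence, and half reluctant, with 40%. An unselected arm shows 0.5 × 0.70 + 0.5 × 0.40 = 55%. Enrolling 60:40 gives 0.6 × 0.70 + 0.4 × 0.40 = 58%; enrolling 70:30 gives 0.7 × 0.70 + 0.3 × 0.40 = 61%. That is 3 to 6 points with no intervention effect.
 - *Assumed shift in means.* Section 2.7 gives 200 per arm and 20% attrition, so 200 × 0.80 = 160 evaluable. Take a simple unadjusted comparison at two-sided 5% (the protocol does not state sidedness). With no true effect and a selection shift of s standard deviations, the chance of a false positive is about Φ(s/√(2/160) − 1.96), where √(2/160) = 0.1118:

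| s (assumed) | s/0.1118 | false-positive rate |
|---|---|---|
| 0.1 | 0.894 | about 14% |
| 0.2 | 1.789 | about 43% |
| 0.3 | 2.683 | about 77% |

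Baseline adjustment would lower these rates by an amount that cannot be computed from the documents.

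**The case against.** A reader might infer that recruiters know every patient's arm before approaching them. The documents do not support that as a fact. They also describe individual allocation after consent, late notification, and duty pharmacists unaware of allocation. A concealed reading is possible: patients are randomised one by one, and the ten randomised pharmacists only deliver care by arm. Section 2.10 lends it some support, since it introduces participants to the intervention-arm facilitator individually by telephone. The abstract's five pharmacies in total, against five plus five in 2.4, also sit more easily with both arms sharing pharmacies. This stands, and the point is therefore conditional.

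Four further limits also stand.

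- The text does not settle that the ten randomised pharmacists are the people who obtain consent. The screening sentence in 2.8 names no one, and the team in 2.4 includes lady health workers (LHWs) and vaccinators.
- One might read 2.4 as pharmacists choosing sites already labelled by arm. The figures in parentheses may only give the resulting split, and non-random choice of sites is ordinary.
- The argument that only intervention staff have telephone work is weak, because 2.6 gives routine calls to both arms. The counselling load and the educational content differ.
- The 70% and 40% strata have no source in the documents. They concern adherence, which 2.14 makes secondary, and they fit poorly with an eligibility list that includes poor adherence.

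None of this reconciles the arm labels on recruiting pharmacies with concealed individual allocation.

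**Conclusion.** The concern holds in conditional form. Sections 2.4, 2.9 and 2.10 contradict each other on how patients receive their arm. If the arm follows the pharmacy or pharmacist, allocation is predictable before screening and the statement in 2.10 is untrue. If allocation is truly individual, the arm labels in 2.4 are wrong or mean something the article does not say. The documents do not show which applies, so failed concealment is not established.

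The size of any resulting bias is unknown. The percentages above rest on assumed inputs and must not be read as estimates. The matter should still be settled before recruitment: selection at enrolment cannot be repaired in the analysis, and as written the trial could be run with predictable allocation and reported as concealed.

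**What to change.** State one unit of allocation and make 2.2, 2.4, 2.9, 2.10 and the abstract agree with it.

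- **If the unit is the individual:** remove the arm labels from the recruiting pharmacies in 2.4. Release each allocation singly from the biostatistician's list, only after eligibility, consent and baseline are recorded. Say that the ten randomised pharmacists only deliver arm-specific care after allocation and take no part in recruitment. Keeping delivery staff separate by arm also limits the contamination that 2.2 names as a concern.
- **If the unit is the pharmacy or pharmacist:** withdraw the concealment statement in 2.10 and the individual label in 2.2. Approach consecutive eligible patients, keep a screening log by pharmacy, and report screened-to-enrolled ratios and baseline characteristics by arm. Where feasible, have existing team members who are not told the arm do screening and consent. The consequences for sample size and standard errors then need their own treatment.

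The cost is a wording change plus either one allocation message per patient or a short log. No extra patients are needed. Screeners unaware of the arm may be hard to provide in pharmacies where arm-specific material is visible, so that step may need some staff time. The second route also means a less favourable description of the design.

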### 2.2. Study Design

This is a two-arm, single-blind, individual, randomized, controlled trial that will determine the effectiveness of pharmacist-led educational interventions for the patients who approached pharmacies with LRTI prescriptions. The present study will be conducted in a community-pharmacy setting in the rural region of Pakistan. The iRCT will be favored to reduce possible contamination between the two groups. The standard protocol items; recommendation for interventional trials (SPIRIT) used in the current trials are presented in Figure 1 and the checklist (Additional File S1).

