### 2.3. Study Setting and Population

Swat, formally known as the ‘Yousufzai State of Swat’ (1849–1969), has a population of 2.3 million at present, and is one of the rural districts in the northern region of the Khyber Pakhtunkhwa, Pakistan. About 86% of the total population lives in rural areas [24,27]. Swat has witnessed extensive militancy/conflict Since 2007 [25]. In 2009, more than 2 million people in the valley became internally displaced persons (IDPs) across Pakistan during the vigorous conflict between the militants and the army [28]. In July 2009, these IDPs were asked to return, after the Government declared the area nonviolent, although the continuous military presence and the intermittent conflicts between security agencies and militants remained, creating social restlessness [26]. Infectious diseases remain high in number. The trial will be carried out in two (Khwazakhela and Janu) union councils in the Swat district, Khyber-Pakhtunkhwa Pakistan. The union council (UC) and neighborhood councils are the basic units in the new local government laws of administration in Pakistan with a population of 2000–10,000 per UC.

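### If pharmacists carry the arm, the allocation described takes no account of the two union councils, so chance imbalance between localities is not rare and could be prevented at almost no cost

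*Protocol article*

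**What the plan says.** Section 2.3 of the protocol article gives the setting: "The trial will be carried out in two (Khwazakhela and Janu) union councils in the Swat district". The number of pharmacies or pharmacists in each UC is not stated.

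Two units of allocation appear. Section 2.2 describes the design thus: "This is a two-arm, single-blind, individual, randomized, controlled trial". Section 2.9 agrees at first: "For every participant that is recruited, a sample 1:1 is used to allocate them into control and interventional groups". It then says that "ten pharmacists will be randomized to the intervention and control arms 1:1 and the permuted method will be used", to be done by the study teams "exchanging a list of pharmacists, each of whom has a unique number assigned to them". Section 2.4 has the trained pharmacists "select pharmacies (5 = control, 5 = interventional) to recruit participants". On these last three statements, arm is a property of the pharmacist or pharmacy.

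UC is not mentioned in the allocation steps of 2.9. It enters in 2.10, which says of pharmacists and teams allocated to control that "they will continue to regularly contact the allocated UC". Section 2.17 lists the terms of the primary mixed model: visit, its interaction with treatment group, baseline scores on the two questionnaires, and a random subject effect. UC and pharmacy are not among them.

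**The concern.** With ten pharmacists in two places, allocation of pharmacists can put most of one locality into one arm. The localities may differ in prescribers, literacy or access to the hospital. Any such difference that bears on beliefs, knowledge or adherence would then appear as an intervention effect, or mask one. None of the listed model terms represents locality, so nothing in the analysis as described would separate the two.

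The wording of 2.10 adds to the doubt, because an allocated UC in the singular, mentioned in a sentence about the control arm, leaves open how UC and arm relate.

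**Working it through.** The plan gives no figure on this point, so there is none to reproduce.

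**Inputs from the protocol article:** 2 UCs (2.3); 10 pharmacists allocated 1:1, hence 5 per arm (2.9, consistent with 5 and 5 pharmacies in 2.4); 200 patients per group and 20% attrition (2.7).

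**Assumptions, not in the article:** the number of pharmacists per UC (a range is shown); equal recruitment per pharmacist; one permutation of all ten, or a list not ordered by UC; the size of any UC difference.

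**1. Chance of imbalance.** Choosing 5 of 10 for intervention gives C(10,5) = 252 equally likely draws. With *a* pharmacists in one UC and *b* in the other, the number of draws placing *x* of the *a* in the intervention arm is C(a,x) × C(b,5−x).

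- 5 and 5: the counts for x = 0 to 5 are 1, 25, 100, 100, 25, 1. A 4:1 or worse split occurs in (1 + 25 + 25 + 1)/252 = 52/252 = 20.6%. Complete separation occurs in 2/252 = 0.8%.
- 6 and 4: the smaller UC falls wholly in one arm in 2 × C(6,1)/252 = 12/252 = 4.8%.
- 7 and 3: 2 × C(7,2)/252 = 42/252 = 16.7%.
- 8 and 2: 2 × C(8,3)/252 = 112/252 = 44.4%.

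**2. What an imbalance does.** Let D be the difference between arms in the share of patients from one UC, and δ the difference in outcome between UCs. Without adjustment, the arm contrast shifts by D × δ.

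| Split, 5 and 5 layout | D | Shift if δ = 10 points | Shift if δ = 0.3 SD |
|---|---|---|---|
| 3:2 | 0.6 − 0.4 = 0.2 | 2 points | 0.06 SD |
| 4:1 | 0.8 − 0.2 = 0.6 | 6 points | 0.18 SD |
| 5:0 | 1.0 − 0 = 1.0 | 10 points | 0.30 SD |

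When the smaller UC falls wholly in one arm, D is 4/5 = 0.8 for the 6 and 4 layout, 3/5 = 0.6 for 7 and 3, and 2/5 = 0.4 for 8 and 2. The most frequent of these events is therefore also the mildest.

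For scale, 200 × 0.8 = 160 completers per arm detect (1.960 + 0.842) × √(2/160) = 0.31 SD at 80% power and two-sided 5%, ignoring clustering. A shift of 0.18 SD is more than half of that.

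**3. Allocation within UC.** With 5 and 5, each UC splits 3:2 or 2:3. Keeping five pharmacists per arm means that the second UC mirrors the first, so D = 0.2. With 6 and 4 the splits are 3:3 and 2:2, and with 8 and 2 they are 4:4 and 1:1, so D = 0. With 7 and 3 they are 4:3 and 1:2, so D = 2/5 − 1/5 = 0.2.

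**4. Why adjustment alone is second best.** In the 5 and 5 layout the correlation between arm and UC equals D, so adjusting for UC multiplies the variance of the arm contrast by about 1/(1 − D²), leaving aside the variance that UC itself explains. That is 1/(1 − 0.04) = 1.04 at 3:2 and 1/(1 − 0.36) = 1.56 at 4:1. At 5:0 the effect cannot be estimated.

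**The case against.** The strongest reply is that the stated design is individual. If every recruited participant is allocated 1:1 within a pharmacy, arm is not systematically tied to locality and the calculation above does not apply. This stands. The point is conditional on pharmacists or pharmacies carrying the arm, and the article supports both readings.

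A reader might go further and infer from 2.10 that one UC is control and the other intervention, so that arm and locality are wholly confounded. The article does not support this. No sentence assigns a UC to an arm. The phrase in 2.10 may simply mean the UC where that team works. The same section places consent and eligibility before random allocation and has participants introduced individually to the intervention facilitator. Section 2.11 speaks of contact in both UCs, although that would be true either way. By chance, complete separation has probability 0.8% in the 5 and 5 layout.

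Three further objections have some weight.

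- A journal article may leave stratification to the full protocol, so its absence is not by itself an error. But the article does describe the pharmacist allocation, and 2.10 contains wording that needs correction in any case.
- Unstratified randomization is valid: the imbalance is a chance event and not a bias in expectation. That is correct, and the shifts shown are conditional on an unlucky draw. With ten units, such draws are common enough to be worth preventing.
- The primary model adjusts for baseline questionnaire scores, which removes part of the locality difference in beliefs and knowledge. Adherence, a secondary outcome in 2.14.2 but the main objective in 2.1, is not covered by those baseline scores.

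The layouts and the UC differences are assumptions. Equal recruitment is also doubtful, since 2.7 recruits as many patients as possible from each pharmacy.

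**Conclusion.** The point holds in conditional form. If pharmacists or pharmacies carry the arm, nothing in the allocation described prevents a poor split between the two UCs. A 4:1 or worse split has probability 20.6% with five pharmacists per UC. With 7 and 3, or 8 and 2, the smaller UC falls wholly in one arm with probability 16.7% or 44.4%. A 4:1 split passes 60% of any UC difference into the arm contrast. These figures assume the layout, equal recruitment, and a permutation that does not happen to balance UC: small blocks of two or four applied to a list ordered by UC would already give only 3:2 or 2:3 splits in the 5 and 5 layout, but the article describes no such ordering.

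If participants are allocated within pharmacies, there is no systematic confounding and only the wording of 2.10 remains to be clarified. Total confounding of arm with locality is not established. This is a design improvement that should be made, not a fatal flaw.

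**What to change.** In 2.9, state which unit is allocated, and make the remedy follow from it.

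- If pharmacists are the unit: run the permuted allocation separately within each UC, so that both arms are present in both, with the odd pharmacist in each UC mirrored to keep five per arm. Add UC as a fixed effect to the model in 2.17.
- If participants are the unit: use permuted blocks within each pharmacy, and remove the control and interventional labels from the pharmacies in 2.4. The two cannot coexist, because a pharmacy labelled by arm has only one arm to allocate.

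In either case, state the number of pharmacies per UC and reword the last sentence of 2.10 so that it does not tie an arm to a UC.

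The cost is that the biostatistician generates the list by stratum and, in the first case, the model gains one term. No extra patients, staff or visits are needed.

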### 2.11. Data Collection

At first, data from patients’ medical records reporting LRTIs (medical notes will be checked for the diagnosis) would be collected by trained pharmacists at community pharmacies, and the pharmacist team will remain blinded to the outcomes. A complete booklet of educational written information will be provided to participants in each interventional arm. The booklet will include materials that are relevant to antibiotic use, such as graphical leaflets, antibiotic dosing regimens kept on sticky notes, adherence, and prevention of antibiotic storage in the home. Following this textual counseling, oral/verbal counseling will be delivered in the patient’s usual area of counseling at a pharmacy. The patient’s information will be transferred to pre-determined data collection forms and stored securely. For the follow-up phase, patients’ valid mobile phone numbers will be collected and retained for future contact and follow-up. The trial team members will contact the participants through their mobile phones in both union councils. After one week, patients will be asked to exhibit their prescribed antibiotics, and the first therapy outcomes will be checked at the beginning of the second week. Finally, in the final session of the trial, a qualitative interview will be scheduled for the 7th week of the study. To keep data quality high, data collection should be current and dependable. As a result, at least three meetings will be held for the field assistance members (pharmacists) to keep the records up to date. The lead investigator will collect all data once a week, as in Table 2.

